### Retention

Retention is addressed at the participant, researcher, and contextual levels [75]. At the participant level, a series of communications was developed to convey appreciation for participation in the trial, e.g., e-cards with brief appreciation videos from investigators at regular intervals, birthday e-cards, and mailed Happy New Year cards. The AMPLIFY logo was incorporated into the design of all communications to ensure easy recognition by participants. At the contextual level, a tracking system shared by assessors and recruiters (who also schedule follow-up assessments) was developed to ensure consistent communication with each participant. At the researcher level, investigators ([name]), recruiters, assessors, and project managers, meet weekly to review recruitment and retention numbers to ensure that participants at risk of drop-out are identified early. Changes to procedures and communications with participants are discussed at these meetings to ease participant burden and reduce drop-out risk. Participants who may need to pause the intervention due to health or personal reasons (e.g., COVID-19, elected/emergency surgeries, deaths in the family, changes of residence, prolonged vacations) are also discussed by project managers and investigators ([name]) to determine when they can resume participation. Outcome data will be collected from all participants, including those who discontinue or deviate from the intervention protocols and are still willing to participate in assessments.

### Statistical considerations

#### Data management, safety and monitoring

Data will be entered into REDCap, a password -protected secure web application for building and managing online surveys and databases with built in range checks for data values and other processes to promote data quality. To protect confidentiality of data, information will be collected from the Web-based surveys, personal identifiers will not be directly linked with the data collected, nor used in any reports, materials, or presentations that emanate from this work. All electronic files containing personal identifiers will be stored only on study staff computers at UAB’s on-site file servers (located behind secure firewalls). Information transferred to the server (for backup purposes) will be done via secure file transfer protocol. Files may be transferred to other computers via the Internet. When this is done, the files will be protected through a method that encrypts their contents during transfer and storage. The on-site file servers are physically accessible only to network support specialists (locked rooms). The on-site file server will be electronically accessible only to study staff and authorized contractors (as part of the research team—not necessarily UAB Employees) through user/password protection. Non-electronic files (i.e., consent forms) will be kept in a locked file cabinet, located in a locked room. Any biological samples will only be labeled with study identification (ID) numbers and the time and date of collection. Access to this room is limited to research staff only. In addition, all research staff are HIPAA certified and have completed and are current with regard to IRB training. Data sets provided as a function of the NIH Data Sharing Requirement will be stripped of identifying information according to HIPAA policy.

An external data safety and monitoring board (comprised of oncology and clinical trial investigators, clinicians, patient advocates; independent from the sponsor and competing interests) and UAB Scientific Monitoring Subcommittee will meet annually to audit trial conduct and review findings, scientific findings, IRB compliance, any adverse events, etc.

#### Sample size and power

Power calculations are based on testing the primary aims for each project, resulting in sample sizes of 130 participants for each of the intervention arms in Projects 1 and 2, and 260 participants for the wait-list control/simultaneous arm. Power calculations for Projects 1 and 2 assume a two-sided two-group chi-square test for groups with unequal sample sizes, and those for Project 3 assume a two-sided two-group chi-square test for groups with equal sample sizes and a 5% significance level. For Project 1, assuming 130 participants for the intervention arm and 260 participants for the wait-list control arm, and that 43.9% of the diet intervention arm and 27.3% of the control arm will lose ≥3% weight yields 90% power to detect a difference of ≥16.6% between study arms as statistically significant [28]. For Project 2, assuming 130 participants for the intervention arm and 260 participants for the wait-list control arm, and increases of participants meeting recommendations of 17.6% for the exercise intervention arm and 3.8% for the control arm based on the BEAT Cancer efficacy trial yields > 95% power to detect a difference of ≥13.8% between study arms as statistically significant [12]. For Project 3, assuming 260 participants/arm and increases in the proportion achieving primary behavioral goals (i.e., improved diet quality, ≥3% weight loss, and ≥ 150 weekly minutes of ≥ moderate intensity aerobic physical activity) of 33.3% for the sequenced arm and 22.2% for the simultaneous arm based on past sequential and simultaneous interactive computer-tailored interventions [76] yields 80% power to detect a difference of ≥11.1% between study arms as statistically significant. Accrual targets assume 20% drop-out. If study dropout for Project 3 is greater than anticipated, we will still have adequate power to detect modest differences between the two study arms. For example, if this project concludes with 200 participants/arm, there will be 80% power to detect a difference of ≥12.5% between study arms as being statistically significant; if the project concludes with 136 participants per arm, there will be 80% power to detect a difference of ≥15% between study arms as being statistically significant.

#### Data analysis

Descriptive statistics will be calculated for all study variables, and normality checks will be performed with subsequent data transformation if indicated prior to data analysis. Statistical tests will be two-sided using a significance level of 5%. Statistical analyses will be conducted using SAS version 9.4 or higher (Cary, NC). Multiple imputation methods may be used to address missing data for variables with moderate amounts of missing data. Formal interim analyses and stopping rules are not planned given the relatively short duration of our intervention and primary aims of behavior change.

#### Primary outcomes

An intent-to-treat analysis will be performed for all primary outcomes (Table 2). The chi-square test will be used to test for differences in the outcomes (proportions) between arms. An exact 95% confidence interval based on the binomial distribution will be determined for the binary outcome (proportion). Logistic regression models will then be used to regress the binary outcome on intervention arm, with pre-specified covariates such as age and gender in order to test for arm differences in the covariate-adjusted outcomes (proportions). For Projects 1 and 2, outcomes will be compared at 6 months. For Project 3, outcomes will be compared immediately post-intervention (12 months for the sequenced arm and 18 months for the simultaneous arm).

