### Randomization

After completion of the baseline assessment, and using a fixed block design, all participants (*n* = 652) are randomized to the sequenced (*n* = 326) or the wait-listed/simultaneous intervention arms (*n* = 326). Sequenced arm participants are then immediately randomized to diet or exercise intervention sequences (*N* = 163 each) for projects 1 and 2. The study flow is depicted in in Fig. 1. The randomization sequence was generated using SAS (Version 9.4, Cary, NC) by an off-site biostatistician. Arm assignment is managed by a central office of blinded staff who have no contact with study participants and implement the computer-generated randomization sequence as baseline assessments are completed.

Participants who are randomized to the wait-list control (followed by the simultaneous intervention), receive brief monthly modules on survivorship topics during the 6-month period they are wait-listed. These modules use the same web-based platform as the other AMPLIFY interventions. Topics are: 1) Good Communication with Physicians; 2) Importance of Quality Sleep; 3) Cognitive Functioning; 4) Benefits of Laughter; 5) Benefits of Creative Arts; and 6) Welcome to the AMPLIFY diet and exercise intervention. This last module serves as an introduction to the simultaneous intervention and addresses next steps and expectations.

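### The first-line primary test is an unadjusted chi-square that makes no use of baseline outcome values as covariates; it is valid, but gives up efficiency, mainly for the diet and activity goals of Project 3

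*Protocol article*

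**What the plan says.** The Primary outcomes section of the protocol article gives the first-line analysis: "The chi-square test will be used to test for differences in the outcomes (proportions) between arms". It continues: "Logistic regression models will then be used to regress the binary outcome on intervention arm, with pre-specified covariates such as age and gender". Age and gender are examples; the list is left open. The section does not say in words which of the two tests decides.

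The Sample size and power section rests on the same test. For Projects 1 and 2 the calculations "assume a two-sided two-group chi-square test for groups with unequal sample sizes", and for Project 3 the equal-groups version. The evaluable numbers are "130 participants for each of the intervention arms in Projects 1 and 2, and 260 participants for the wait-list control/simultaneous arm". The Data analysis section sets a two-sided 5% level.

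The baseline data will exist for everyone randomised. The Randomization section opens "After completion of the baseline assessment, and using a fixed block design, all participants", so the baseline assessment comes first. Table 2 lists diet quality (HEI-2015 from two recall days), accelerometer activity over 7 days and measured weight as the primary outcomes, and the Overview has assessments at baseline and every 6 months. For the secondary outcomes, the plan does bring baseline and post-intervention measurements into mixed models.

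**The concern.** Whether a participant reaches 150 minutes a week at follow-up, or shows better diet quality, is likely to depend on where that participant started. A test that leaves the starting value out treats that predictable variation as noise. It also leaves any chance baseline difference between arms in the comparison. The trial has already paid for the baseline measurements.

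Project 3 is where this could matter. It carries the overarching question of sequenced against simultaneous delivery, it has the lowest planned power, and the article itself considers dropout worse than the assumed 20%. A few points of power at no recruitment cost would be a useful reserve.

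**Working it through.** **1. Reproduce the plan's power figures.** Inputs, all from Sample size and power: Project 1, 43.9% vs 27.3% with 130 and 260; Project 2, 17.6% vs 3.8% with 130 and 260; Project 3, 33.3% vs 22.2% with 260 per arm; two-sided 5%.

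Let d = p1 − p2 and p̄ be the pooled proportion. Then SE0 = √[p̄(1 − p̄)(1/n1 + 1/n2)], SE1 = √[p1(1 − p1)/n1 + p2(1 − p2)/n2], and power = Φ[(d − 1.96·SE0)/SE1].

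| Project | d | p̄ | SE0 | SE1 | (d − 1.96·SE0)/SE1 | Power | Stated |
|---|---|---|---|---|---|---|---|
| 1 | 0.166 | 0.3283 | 0.0504 | 0.0516 | 1.302 | 90.4% | 90% |
| 2 | 0.138 | 0.0840 | 0.0298 | 0.0354 | 2.246 | 98.8% | >95% |
| 3 | 0.111 | 0.2775 | 0.0393 | 0.0390 | 0.873 | 80.9% | 80% |

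The dropout inflation also fits: 130/0.8 = 162.5, so 163, and 260/0.8 = 325, against 326 = 2 × 163 planned. The trial is sized for the test it names.

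**2. Add the baseline value.** The correlation ρ between baseline and the latent follow-up outcome is not in the article, so it is an assumption shown over a range. Model: a latent normal outcome is cut so that each arm has its stated rate, with a standard normal baseline covariate of correlation ρ. The Pearson chi-square is compared with the likelihood-ratio test of arm in a logistic regression on arm and baseline. There were 3,000 simulated trials per cell, with a Monte Carlo standard error of about 0.7 point or less (√(0.8 × 0.2/3000) = 0.0073). For Project 3 the stated rates are applied to a single binary goal.

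| ρ | Project 1: chi-square → adjusted | Project 2 | Project 3 |
|---|---|---|---|
| 0.1 | 90.1% → 90.2% | 99.3% → 99.2% | 80.3% → 80.7% |
| 0.3 | 90.4% → 91.6% | 99.1% → 99.2% | 81.6% → 83.8% |
| 0.5 | 90.0% → 93.9% | 99.2% → 99.4% | 80.7% → 86.5% |
| 0.7 | 90.9% → 97.6% | 99.5% → 99.9% | 80.3% → 91.4% |

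At ρ = 0 there is no gain. Separate simulations of the same kind for Project 3 gave 82-83% adjusted power at 0.3 and about 93% at 0.7, so the range of roughly 82-92% is stable to a point or so.

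The Project 1 column needs care. The endpoint is percentage weight loss, and baseline weight probably predicts it only weakly, so the rows for 0.1 and 0.3 are the relevant ones: 0.1 and 1.2 points.

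**3. Two features that could shrink the Project 3 gain.**

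*Goals defined as a change.* With equal variances at the two visits and correlation r between them, change correlates with baseline at −√[(1 − r)/2], which is −0.5 at r = 0.5. Defining the goal as a change therefore does not remove its dependence on baseline. Simulated at the Project 3 rates:

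| r | Chi-square → adjusted | Gain (points) |
|---|---|---|
| 0.4 | 80.3% → 87.4% | 7.1 |
| 0.5 | 82.5% → 87.9% | 5.4 |
| 0.6 | 82.1% → 85.6% | 3.5 |
| 0.7 | 80.7% → 84.2% | 3.5 |

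*Restricted baseline activity.* Eligibility requires under 150 minutes a week. Removing the top 20% of baseline values (an assumption) gives:

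| r | Chi-square → adjusted | Gain (points) |
|---|---|---|
| 0.4 | 81.0% → 82.7% | 1.7 |
| 0.5 | 80.7% → 83.8% | 3.1 |
| 0.6 | 80.3% → 86.1% | 5.8 |
| 0.7 | 81.4% → 88.3% | 6.9 |

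Follow-up is also later in one arm (18 months against 12). With r = 0.5 in one arm and 0.3 in the other, power goes from 81% to 85%.

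**The case against.** The strongest reply is that nothing here is wrong. An unadjusted chi-square is valid in a randomised trial, the trial was sized for it, and the sizing reproduces. That stands in full: a reader might infer an invalid test or a power shortfall, and the document supports neither.

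A reader might also infer that the primary analysis ignores baseline altogether. That goes too far. Weight loss above 3% is measured against each person's own starting weight, and improved diet quality reads as a change as well. Activity is an absolute threshold, but entrants must be below it at screening. What stands is narrower: the baseline value is not used as a covariate in the first-line test, and a change-defined goal still depends on it.

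A third reply is that the covariate list is illustrative and the full list commonly sits in an analysis plan not shown here. That is fair for the logistic model, and its omission of baseline is not shown. It does not help the chi-square, which takes no covariates and is listed first.

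Which test decides can reasonably be inferred: the chi-square comes first and carries the power calculation. Saying so outright would be a clarification; there is no contradiction to resolve.

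Two further inferences should be resisted. One is a useful gain in Project 2: at the stated rates power is about 99% either way. The other is that randomisation is unstratified: the Randomization section mentions a fixed block design and neither states nor excludes stratification.

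**Conclusion.** The point holds as a missed efficiency gain. The first-line primary test is unadjusted although the baseline value of every primary outcome is collected before randomisation.

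The benefit is concentrated in the diet and activity goals of Project 3. Power there would rise from about 80% to roughly 82-92% if the baseline to follow-up correlation is 0.3 to 0.7, with almost nothing gained at 0.1. Under a change-defined goal or a truncated baseline the gain is about 2 to 7 points at correlations of 0.4 to 0.7. For Project 2 it is at most 0.4 point, and for weight loss it is likely to be small.

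These sizes rest on a latent normal model, on correlations the article does not give, and on applying the Project 3 rates to one binary goal at a time. The change is worth making because it is nearly free; the trial does not depend on it.

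**What to change.** For each primary endpoint, name one decisive test: a logistic regression on arm, the continuous baseline value of that outcome (accelerometer minutes, HEI-2015 score or weight), age and sex. Because an adjusted odds ratio is not the difference in proportions on which the trial was sized, report the marginal risk difference from that model with its 95% CI. Keep the chi-square as the unadjusted supporting analysis and label it so.

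Fix this before outcomes are compared by arm. It costs a few sentences in the analysis plan and a matching change to the protocol's Primary outcomes section. Sample size, visits and data collection are unchanged, and the existing power statements can stay as a conservative basis.

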#### Secondary outcomes

Analyses of secondary outcomes (Table 2) will account for comparisons of the two study arms (between-group comparisons) as well as the baseline and post-intervention measurements of each participant (within-arm comparisons). Since most of these outcomes are continuous, the primary method of analysis for these outcomes will be mixed models repeated measures analysis. This method will allow us to compare changes over time (within-group changes) and differences between groups simultaneously. An appropriate structure for the covariance matrix will be selected based on the final data. The Tukey-Kramer multiple comparisons test will be used as the post hoc test. These models will include terms for group, time, and group x time, as well as terms for any other covariates and interactions that are of scientific interest such as age, sex, race/ethnicity and rural status. Additional general linear mixed models may also be used. Overall unadjusted between-group comparisons at baseline may be performed using the two-group t-test, and overall unadjusted within-group comparisons between two time points may be performed using the paired t-test.

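### The mixed model for the continuous secondary outcomes leaves each arm a free baseline mean, so it gives up precision that the pre-randomisation baseline could supply at no cost

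*Protocol article*

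**What the plan says.** The Secondary outcomes section of the protocol article states that "the primary method of analysis for these outcomes will be mixed models repeated measures analysis". The analysis is to cover the comparison of the two arms "as well as the baseline and post-intervention measurements of each participant", so baseline is one of the repeated responses. On the mean model it says "These models will include terms for group, time, and group x time", and then admits "any other covariates and interactions that are of scientific interest such as age, sex, race/ethnicity and rural status". The baseline value of the outcome is not among the named covariates, and no common baseline mean across arms is imposed. The stated aim is broad: "This method will allow us to compare changes over time (within-group changes) and differences between groups simultaneously". No single contrast is named as the treatment test.

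The Randomization section fixes the order of events: "After completion of the baseline assessment, and using a fixed block design, all participants" are allocated to their arms. Baseline is therefore a pre-randomisation measurement for everyone.

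**The concern.** With baseline in the response, an arm effect, a visit effect and their interaction give every arm its own mean at every visit, baseline included. The model then estimates a baseline arm difference that randomisation has already set to zero in expectation. With complete data and no further covariates, the two natural arm contrasts become unadjusted ones: the interaction is the difference in mean change, and the arm difference at follow-up is the difference in raw follow-up means. Baseline is in the model, but it does not act as an adjustment.

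What is at stake is the width of the confidence intervals, and so the chance of detecting real effects, on the continuous outcomes listed as secondary in Table 2: waist, physical performance, blood pressure, muscle mass, biomarkers and patient-reported scores. Diet quality, activity and weight are also affected in the projects where they are secondary.

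**Working it through.** **The plan's own figures.** The only power figures given are for the binary primary aims (Sample size and power). A two-sided 5% pooled chi-square calculation reproduces them: Project 1, 90.4% (stated 90%); Project 2, 98.8% (stated above 95%); Project 3, 80.9% (stated 80%). Dropout of 20% gives 130/0.8 = 162.5, so 163, and 260/0.8 = 325, against the 163 and 326 randomised. There is no power figure, SD or correlation for any continuous secondary outcome.

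**Inputs.** From the article: two-sided 5%; 163 versus 326 randomised in Projects 1 and 2; 20% dropout. Assumed: equal SD at both visits, and a baseline to follow-up correlation rho, shown from 0.3 to 0.9. The 80% power reference is a yardstick, not a claim of the plan.

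**Step 1: what the stated model estimates.** One generated data set was used, with 130 versus 260 participants, four visits and no missing data. The generalised-least-squares interaction contrast equalled the raw difference in mean change (0.00217 both ways). The arm contrast at follow-up equalled the raw difference in follow-up means (0.01725 both ways).

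**Step 2: variances with complete data**, in units of SD² × (1/n1 + 1/n2):

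- change contrast: 2(1 − rho)
- follow-up contrast: 1
- baseline-adjusted (common baseline mean, or baseline as covariate): 1 − rho²

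The adjusted variance is therefore (1 − rho²)/[2(1 − rho)] = (1 + rho)/2 of the change-contrast variance, and 1 − rho² of the follow-up-contrast variance.

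**Step 3: power.** If the stated contrast has 80% power, the adjusted one has Φ((1.96 + 0.8416)/√ratio − 1.96). At rho 0.5 the ratio is 0.75, and 2.8016/0.866 − 1.96 = 1.275, which gives 90%.

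| rho | Ratio to change | Power | Ratio to follow-up | Power |
|---|---|---|---|---|
| 0.3 | 0.65 | 94% | 0.91 | 84% |
| 0.5 | 0.75 | 90% | 0.75 | 90% |
| 0.7 | 0.85 | 86% | 0.51 | 98% |
| 0.9 | 0.95 | 82% | 0.19 | above 99% |

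**Step 4: 20% missing follow-up, 163 versus 326.** The likelihood now recovers some baseline information. The variance factors are:

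- free-mean change contrast: (1 − rho²)/0.8 + (1 − rho)²
- adjusted contrast: (1 − rho²)/0.8

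At rho 0.5 these are 0.9375 + 0.25 = 1.1875 and 0.9375, a ratio of 0.79. Since 1/163 + 1/326 = 0.00920, the standard errors are √(1.1875 × 0.00920) = 0.1045 and √(0.9375 × 0.00920) = 0.0929 SD. Multiplied by 2.8016, the differences detectable with 80% power are 0.29 and 0.26 SD. At a ratio of 0.79, 80% power becomes 88%.

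At rho 0.3, 0.5, 0.7 and 0.9, the free-mean standard error is 1.20, 1.13, 1.07 and 1.02 times the adjusted one for the change contrast, and 1.04, 1.13, 1.33 and 2.10 times for the follow-up contrast. A loss remains throughout.

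**The case against.** The strongest reply is that nothing here is an error. The stated model is a standard, valid analysis, and the choice is between two valid models. The article is condensed, its covariate list is open, further mixed models are allowed, and the exact parameterisation could be settled in an analysis plan that is not shown. Only secondary outcomes are involved, no stated power figure changes, and the size of the loss rests on a correlation that the article does not give.

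Most of this stands and limits the point, but it does not remove it. The article fixes the terms of its primary method for these outcomes, and those terms leave the baseline means free. The open wording permits baseline adjustment without specifying it. Adding the baseline value as one more covariate while it also remains a response would not be a proper adjustment.

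Two further limits also stand. Equality with the plain contrasts is exact only with complete data and no further covariates, and the plan expects both dropout and covariates. The large losses at high correlation arise only if the follow-up contrast is the test, which the article does not say. The two contrasts lose most at opposite ends of the range, so the two large losses do not occur together.

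**Conclusion.** The point holds as a free gain in precision for the continuous secondary outcomes. Against the change contrast it is worth about 14 percentage points of power at rho 0.3 and 2 points at rho 0.9, from an 80% reference. Against the follow-up contrast the pattern reverses: small at low correlation, large at high. In Projects 1 and 2, at rho 0.5 with 20% dropout, it moves the detectable difference from about 0.29 to 0.26 SD. All of this rests on the assumed rho and on equal SDs.

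A reader might infer more, and the article does not support it:

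- **Bias or inflated type I error.** Neither follows. The change contrast does over-correct a chance baseline imbalance and the follow-up contrast leaves it uncorrected, but that describes behaviour given an observed imbalance. Over randomisation both are unbiased.
- **Damage to the primary results or the sample size.** The primary outcomes use chi-square and logistic regression, and the stated power figures are untouched.
- **A benefit from participants with baseline only.** With a common baseline mean they add nothing to the arm contrast: in Step 4 the adjusted variance depends only on the 80% with follow-up. This is no reason to prefer one form of the fix.

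**What to change.** Amend the model sentence in Secondary outcomes in one of two ways:

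1. Keep baseline as a response, but constrain the arms to one common mean at the pre-randomisation (month 0) baseline, fitting visit and arm × post-baseline visit.
2. Model only post-baseline values, with the month 0 value and its interaction with visit as covariates.

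In either case, name the baseline-adjusted arm difference at the endpoint as the test: 6 months for Projects 1 and 2.

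Project 3 needs its own sentence, because the Primary outcomes section compares arms immediately after intervention, at 12 months (sequenced) and 18 months (simultaneous), and a same-visit arm difference would not give that comparison. Use the month 0 baseline in both arms, and either code the response as post-intervention or form the 12- versus 18-month contrast explicitly. Do not impose a common mean at the wait-list arm's month 6 visit: it falls after randomisation, so randomisation does not justify one there.

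The cost is a few sentences and a small change to the SAS code. No new data, sample size change or assumption beyond randomisation is needed.
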